#### Brain imaging

A brain magnetic resonance imaging (MRI) scan will be performed at baseline on a 3.0 Tesla MRI scanner with a 32-channel head coil (Hercules, Philips Medical Systems, Best, The Netherlands). The imaging protocol consists of structural MRI for the anatomical characterization of the brain lesion (i.e., lesion timing, location and extent) and diffusion-weighted imaging (dMRI) to investigate white matter structural connectivity. For children up to the age of 10 years old and in case of anxiety for the MRI assessment, a familiarization protocol will be performed before the actual scan to introduce important characteristics of the assessment (e.g., noise, small space, lying still, headphones for communication) [100]. Furthermore, all participants will be allowed to watch a video of their choice during the entire scan.

##### Structural MRI

High-resolution T1-weighted images will be acquired with the following parameters: echo time = 4.2 ms, repetition time = 9.1 ms, inversion time = 760.3 ms, field of view = 256 FH × 180 RL × 242 AP mm^3^, voxel size = 0.9 × 0.9 × 0.9 mm^3^, and 3D turbo spin echo. In addition, T2-weighted fluid-attenuated inversion recovery images will be acquired with the following parameters: echo time = 283 ms, repetition time = 4800 ms, inversion time = 1650 ms, field of view = 250 FH × 200 RL × 250 AP mm^3^, and voxel size = 1.0 × 1.0 × 1.0 mm^3^. Lastly, also T2-weighted images will be collected with the following parameters: echo time = 280 ms, repetition time = 3000 ms, inversion time = 548 ms, field of view = 256 FH × 198 RL × 256 AP mm^3^, and voxel size = 1 × 1 × 1 mm^3^.

The MRI classification system (MRICS) will be applied to the anatomical images in order to classify the brain lesions according to the timing of the lesion and the predominant lesion pattern, resulting in five main groups: (1) maldevelopments, (2) predominant white matter injury, (3) predominant gray matter injury, (4) miscellaneous, and (5) normal findings [101]. Next, lesion location and extent will be evaluated in more detail using the semi-quantitative MRI (sqMRI) scale developed by Fiori et al. [102, 103]. In short, the sqMRI scale consists of a graphical black and white template on which the lesion is drawn. This template is then used to quantitatively analyze the lesion characteristics, resulting in different global and subscores that separately assess both hemispheres, different brain regions and depths. More detailed information regarding the MRICS and sqMRI can be found in earlier publications [101, 102].

##### Diffusion-weighted images.

Multi-shell diffusion-weighted images will also be acquired using a 2D single-shot spin echo sequence with the following specifications: slice thickness = 2.3 mm, echo time = 93 ms, repetition time = 3765 ms, anterior–posterior phase encoding direction, b-values = 0/1000/25000 s/mm2 with 3/50/74 uniformly distributed gradient direction respectively, in-plane parallel acceleration factor = 1.5 [104], field of view = 136 FH × 240 RL × 240 AP mm3, voxel size = 2.2 × 2.2 × 2.2 mm3, acquisition time = 8 min. There were 124 uniformly distributed diffusion directions. dMRI will be pre-processed using an MRTrix-based pipeline [105]. Constraint spherical deconvolution will be applied to delineate the motor and somatosensory tracts for both hemispheres (e.g., corticospinal tract, thalamic radiations, medial lemniscus) [106, 107].

### Plans to promote participant retention and complete follow-up {18b}

To avoid dropouts due to practical considerations, the scheduling of therapy and assessment sessions will be adapted to the participant’s preferences where possible. Furthermore, one contact person will be appointed to coordinate the scheduling of therapy and assessments and to resolve any questions. Lastly, parents will be contacted after the first week of therapy and halfway the intervention period to discuss feasibility of the therapy and the progress the child has made. In case of deviations from the study protocol (e.g., missed therapy sessions due to illness), the assessments will still be scheduled as described above and the specific deviation will be noted.

### Data management {19}

All data, including assessment results, video recordings, and activity logs, will be digitalized and stored pseudonymized on a secured university network and/or on the REDCap platform. To ensure data quality, double data entry will be performed by two independent researchers. Any discrepancies will be checked and adjusted by a third researcher using the Data Comparison Tool of the REDCap platform. Moreover, range checks will be built-in on REDCap for all quantitative outcome measures. Anomalies and data outliers will be inspected and adapted when appropriate before data analysis. The final trial dataset will be accessible on REDCap to the day-to-day management team.

### Confidentiality {27}

An individual, study-specific identifier will be assigned to all participants upon enrollment to guarantee confidentiality. Next, a participant identification record will be generated, containing personal information, and contact details. This record will be stored separately and access will be restricted to two researchers, who will also be responsible for the pseudonymization. No identifiable or personal data will be published or made available to other researchers. The de-identified dataset will be made publicly available upon publication of the study results via KU Leuven Research Data Repository.

### Plans for collection, laboratory evaluation and storage of biological specimens for genetic or molecular analysis in this trial/future use {33}

N/a—No biological samples for genetic or molecular analysis will be collected.

## Statistical methods

### Statistical methods for primary and secondary outcomes {20a}

All observations will be summarized as mean and standard deviation or median and interquartile range, according to the nature of the data. Baseline comparability between groups will be visually checked based on descriptive statistics. As the participants will be randomized to the intervention or control group, statistical testing of baseline differences will not be performed [108]. To study the time effects of the intervention and to allow for comparison between both groups, linear or generalized mixed models will be applied for the primary and secondary outcome measures. By using random effects, such models correct for the relation among repeated observations within subjects. An additional benefit of these models is that they provide a valid inference for missing values that are (completely) at random [109]. In case the data of an outcome measure is not normally distributed based on the Shapiro–Wilk test and/or visual inspection of the data distribution, transformations will be applied. The main endpoint will be to investigate if there is a difference in evolution of the AHA score over time between both groups. As such, interactions between therapy and time will be analyzed to test for differences in improvements over time between both groups (time*group interaction effect). When a significant interaction is identified, time trends will be tested in both therapy groups separately (time-effect). When the interaction is not significant, the main effect of time will be explored. Effect sizes for the full models will be further calculated using the Cohen’s partial η^2^ formula [partial η^2^ = (F × df_between_)/((F × df_between_) + df_within_)] [110]. Significant time trends will be further investigated with pairwise post hoc tests to compare individual time points (*T*_0_–*T*_1_, *T*_1_–*T*_2_, *T*_0_–*T*_2_). For the model of the primary outcome measure, the post hoc analysis will be Bonferroni corrected and the pairwise post hoc test for *T*_0_–*T*_2_ will be the primary outcome. For the models of secondary outcome measures, a false discovery rate with an adjusted *p*-value of 0.05 will be implemented. Effect sizes of these comparisons will be calculated using Cohen’s d formula [111]. For the second research objective, we will investigate predictive factors of therapy response. Both behavioral and neurological characteristics, i.e., somatosensory function at baseline, attentional functioning, and thalamic volume, will be included as covariates in the model for the primary outcome measure. All statistical analyses will be performed in SPSS Statistics for Windows. Level of significance will be set at 0.05, two-sided. When needed, adapted statistical techniques will be applied in close collaboration with Leuven Biostatistics and statistical Bioinformatics Centre (L-BioStat).

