**Primary outcome**					
	**Bimanual performance**	*(Adolescent) Assisting Hand Assessment (AHA/Ad-AHA)*	Change over time	Logit-based total score (0–100)	*T*_0_, *T*_2_

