### Sample size {14}

The sample size calculation is based on the primary objective, which is defined as the retention of therapy effects on the primary outcome measure being bimanual performance measured with the Assisting Hand Assessment (AHA) at 6 months follow-up. The smallest detectable difference has been reported to be 5 AHA units [62]. Based on a previous intervention study in children with uCP [46], a standard deviation of 5.5 AHA units for improvements after intensive upper limb therapy was calculated by taking the average of the standard deviations between baseline and post-intervention and baseline and follow-up of both intensive therapy groups. The sample size estimate was calculated with G*Power for the following statistical test “Means: Difference between two independent means (two groups)” [63, 64]. With an estimated difference of 5 AHA units in the mean improvement between the intervention and control group and a standard deviation of 5.5 AHA units for both groups, an effect size of 0.9 was calculated. Based on an effect size of 0.9, an alpha level of 0.05 and a statistical power of 0.80, a sample size of at least 21 participants is needed in each group to detect a difference equal to or larger than the smallest detectable difference of 5 AHA units between groups. This number will be increased to 25 per group to account for inevitable dropouts and to maximize the study sample for prediction purposes.

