##### Primary outcome measure

Assisting Hand Assessment, Adolescent Assisting Hand Assessment

The AHA and Adolescent Assisting Hand Assessment (Ad-AHA) evaluate the spontaneous use of the more impaired upper limb during bimanual activities [69, 70]. A semi-structured play session with standardized toys and materials that require the use of both hands is performed and video recorded. Subsequently, 20 items are scored on a 4-point Likert scale ranging from 1 (‘does not do’) to 4 (‘effective use’) and a logit-based total score in AHA units is calculated. The AHA and Ad-AHA have shown to be reliable and valid assessments for children and adolescents with uCP [71–74]. The AHA or Ad-AHA will be evaluated at each timepoint, depending on the age of the participant. The AHA will be the primary outcome measure for this intervention study, because the ultimate aim is to improve the use of the impaired upper limb during daily life activities.

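### Transformation of the primary AHA score depends on normality of the outcome data rather than of the model residuals, so the data could move the primary contrast off the AHA-unit scale

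*Protocol article*

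**What the plan says.** The section Statistical methods for primary and secondary outcomes {20a} states that "linear or generalized mixed models will be applied for the primary and secondary outcome measures", with random effects for the repeated visits. The distributional check is tied to the outcome itself: "In case the data of an outcome measure is not normally distributed based on the Shapiro–Wilk test and/or visual inspection of the data distribution". The consequence is not optional: "based on the Shapiro–Wilk test and/or visual inspection of the data distribution, transformations will be applied". Neither residuals nor random effects are named as the thing to check. No transformation is specified, and nothing says how a transformed result would be brought back to AHA units.

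The same section says that "the pairwise post hoc test for *T*_0_–*T*_2_ will be the primary outcome". Under Primary outcome measure in {18a}, "a logit-based total score in AHA units is calculated", and Table 1 gives the metric as change over time on a 0–100 scale. Sample size {14} is set "to detect a difference equal to or larger than the smallest detectable difference of 5 AHA units between groups", with an SD of 5.5 AHA units for the improvement. Sequence generation {16a} shows that the sample spans MACS I, II and III, two age bands and two levels of tactile impairment.

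**The concern.** The check looks at the wrong quantity. A linear mixed model assumes that the residuals and the random effects are normal, given the fixed effects. It does not assume that the pooled or per-visit scores are normal. A sample drawn from three MACS levels is a mixture, and its raw scores can be clearly non-normal while within-child errors are exactly normal. If all visits go into one test, the repeated scores are also not independent, which Shapiro–Wilk requires.

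The stake is the scale of the primary result. The 5-unit difference, the SD and the sample size are all in AHA units, a scale that is already logit-based. After a non-linear transformation the time-by-group contrast measures something else, and whether that happens, and with which transformation, would be settled by the observed data.

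**Working it through.** **1. The plan's own figure.** Inputs from Sample size {14}: difference 5, SD 5.5, alpha 0.05 (two-sided, per {20a}), power 0.80. Effect size d = 5/5.5 = 0.909, which the article rounds to 0.9. Two-sample t-test with noncentrality d·√(n/2) and 2n − 2 degrees of freedom:

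- d = 0.9, n = 20 per group: power 0.792
- d = 0.9, n = 21 per group: power 0.812
- d = 0.9, n = 25 per group: power 0.877

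The stated 21 per group is reproduced. It belongs to the AHA-unit scale.

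**2. What a transformation does to 5 units.** Log is used as an example only, since the article names no transformation. From a baseline of 30, ln(35/30) = 0.154. From a baseline of 85, ln(90/85) = 0.057. The same gain counts 0.154/0.057 = 2.7 times as much in the lower child, so a contrast on that scale has no single translation into 5 AHA units.

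**3. How often the check fires when the model is right.** Simulated score = MACS-level mean + child effect N(0, s²) + visit error N(0, 5.5²/2), plus 5 units at T2 in one arm. There are 50 children and 3 visits. The visit-error SD of 5.5/√2 = 3.9 gives a change SD of 5.5, as in {14}. MACS means, s and the MACS mix are assumptions, because the article gives none. Shapiro–Wilk rejection at 0.05 in 3,000 trials per row:

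| MACS means; mix; s | all visits pooled | T0 only | T0–T2 change, centred by arm | within-child residuals |
|---|---|---|---|---|
| 75/60/45; equal thirds; 6 | 0.72 | 0.20 | 0.05 | 0.04 |
| 80/62/45; 35/45/20%; 6 | 0.58 | 0.10 | 0.05 | 0.04 |
| 75/60/45; 40/40/20%; 8 | 0.46 | 0.08 | 0.05 | 0.04 |
| 60/60/60 (no mixture); 12 | 0.28 | 0.05 | 0.05 | 0.03 |

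The last row shows that part of the pooled figure comes from non-independence, not from the MACS mixture. The mix matters too: with 75/60/45 and s = 6, moving from equal thirds to 35/50/15% lowers pooled rejection from 0.72 to 0.34 and T0 rejection from about 0.20 to 0.05. Means of 80/60/40 with s = 6 and equal thirds raise them to about 0.95 and 0.46. Across all scenarios examined the ranges are about 25–95% pooled, 5–47% at T0 and about 5% on change.

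**4. Effect on the T0–T2 comparison.** t-test on change between arms, 25 per group, means 75/60/45 or 80/60/40, s of 6 or 8, equal thirds or 35/50/15%, scores below 1 set to 1 before taking logs:

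- *No treatment difference:* rejection is about 4–6% in AHA units, after a log transform, and under the rule of taking logs if the pooled test rejects.
- *True 5-unit difference, AHA units:* power 0.87–0.90, in line with the 0.877 in step 1.
- *True 5-unit difference, log scale, control arm unchanged:* 0.82–0.86.
- *True 5-unit difference, log scale, both arms also gaining 3 to 5 units:* 0.72–0.82, typically 0.74–0.80. Some gain in the control arm is what the article's hypotheses in Objectives {7} expect.
- *Taking logs only if the pooled test rejects:* 0.75–0.88 over these settings.

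**The case against.** The best defence is that the wording is common shorthand in a condensed article, and that a full protocol or analysis plan may say that residuals are meant. It also leaves room for judgement through visual inspection, foresees generalized models, and promises support from the biostatistics centre. Table 1 gives the metric as change over time, and a check on change would fire at only the nominal 5%. AHA-unit means and SDs will be reported in any case.

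Much of this stands as a limit on size. The article does not say that visits are pooled, so a reader who infers that the rule would probably fire goes beyond the text: the high pooled rates depend on that reading and on an assumed MACS mix. A reader might also infer that a transformation could produce a false time-by-group effect. In a randomised trial with no treatment difference, both arms share the same joint distribution of T0 and T2, a common transformation preserves that equality, and the simulated type I error stays near 5%. Nor is it shown that every transformation would lack a basis: if residuals are also non-normal, one may be reasonable.

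What does not stand is that this is merely detail left to another document. The article states a rule, the rule names the outcome data, and its consequence is mandatory. An analysis plan that checks residuals would have to depart from it.

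**Conclusion.** The point holds as a minor one. The trigger for transformation is placed on the wrong quantity and the AHA is not protected from it, so the scale of the primary contrast is left to the data, although the target difference and the sample size are fixed in AHA units. The harm, if the rule fires, is to interpretation and prespecification, with a possible loss of power: from about 0.88 to 0.74–0.80 in the log example when both arms also improve by a few units, and less when the control arm does not. Type I error under no treatment difference is not inflated, and 21 per group remains correct. The rejection rates and powers rest on assumed MACS means, between-child SDs, MACS proportions and control-arm gain, and on log as the example transformation. The reasoning about residuals and scale does not depend on those assumptions.

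**What to change.** Amend the rule in {20a} along these lines:

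- The primary AHA analysis is done untransformed, in AHA units.
- Normality is assessed on the residuals and random effects of the fitted model, mainly graphically.
- If the assumption is clearly violated, the AHA-unit contrast remains primary, and a bootstrap, permutation or transformed analysis is added as sensitivity only.
- Ordinal or bounded secondary outcomes use the generalized mixed models already foreseen.

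The cost is a few lines of analysis wording and slightly more analysis work. Sample size, visits and data collection do not change. Recruitment is planned to run until 30 June 2027 at the latest (Trial status), so the change can be made well before analysis.

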## Assignment of interventions: allocation

### Sequence generation {16a}

After enrollment and prior to the baseline assessment, participants will be assigned to the intervention or control group through randomization by minimization with an allocation ratio of 1:1. A minimization technique will be used to enhance homogeneity between both groups. To diminish allocation prediction, an additional random component of 80% probability will be implemented. The first participant, and in case the marginal totals are equal between both intervention groups, simple randomization will be performed. Participants will be stratified based on age (2 levels: < 11 years and ≥ 11 years), manual ability (3 MACS-levels: I, II, and III) and tactile impairment (2 levels: mild or moderate-severe – flowchart shown in Fig. 3).

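### The primary AHA analysis as described does not use the three minimization factors; if they predict AHA change, its standard error is conservative and some power is forgone

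*Protocol article*

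**What the plan says.** Under Sequence generation {16a} the protocol plans "randomization by minimization with an allocation ratio of 1:1". The stated purpose is balance: "A minimization technique will be used to enhance homogeneity between both groups". Predictability is limited because "an additional random component of 80% probability will be implemented". The factors are given as "Participants will be stratified based on age (2 levels: < 11 years and ≥ 11 years), manual ability" in three MACS levels, and "tactile impairment (2 levels: mild or moderate-severe". Together they carry 1 + 2 + 1 = 4 degrees of freedom.

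Under Statistical methods for primary and secondary outcomes {20a}, "linear or generalized mixed models will be applied for the primary and secondary outcome measures". Random effects account for the repeated measurements, and the between-group test is given as "interactions between therapy and time will be analyzed to test for differences in improvements over time between both groups (time*group interaction effect". The only covariates named in that section are these: "somatosensory function at baseline, attentional functioning, and thalamic volume, will be included as covariates in the model for the primary outcome measure". They are introduced for the objective on predictors of response. Baseline somatosensory function overlaps with the tactile factor. Age and MACS level appear in no described model.

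The Sample size section {14} rests on an unadjusted comparison of mean AHA improvement between two groups: difference 5 units, SD 5.5, 21 per group, raised to 25.

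**The concern.** Minimization makes the arms more alike on its factors than chance would. If a factor predicts the outcome being tested, the estimated group difference varies less over repeated allocations than an unadjusted model assumes. The model leaves the factor's variance in its error term, so the standard error is too large, the test rejects too rarely under the null, and part of the benefit of balancing is not collected.

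The outcome being tested is a change from T0 to T2. A factor that only shifts a child's AHA level by the same amount at every visit cancels from that change. What matters is whether age, MACS level or tactile impairment predicts how much a child changes.

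The Objectives section gives some reason to expect this for one factor: it anticipates a better response in children with worse somatosensory function at baseline. That expectation is argued from the content of the somatosensory therapy, so it may apply mainly to one arm, and no size is attached to it.

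**Working it through.** **Inputs from the protocol.** Difference 5 AHA units, SD of change 5.5, two-sided alpha 0.05, 21 or 25 per group, minimization with an 80% random component, factors with 2, 3 and 2 levels.

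**Assumed inputs.** R2, the share of AHA change variance explained by the three factors, from 0 to 0.30. The prevalence of each factor level is also assumed. The protocol gives neither.

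**1. The plan's own figure.** A two-sided two-sample t-test with the noncentral t distribution and d = 0.9 (or 5/5.5) needs 21 per group. Power at d = 0.9 is 0.812 with 21 per group and 0.877 with 25. The stated figure is reproduced.

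**2. Main effects alone.** Random-intercept mixed models were fitted to simulated trials with time, group and time*group, with and without the factors as main effects. With complete data the T2 time*group estimate and its standard error did not move: in one data set 3.5507 (SE 1.5739) both ways. With 16% of T2 values missing (21 of 25 completing is 1 - 21/25 = 16%), the standard error moved by under 0.5%, for example 1.6120 to 1.6153. The factors must interact with time to affect the primary contrast.

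**3. Factors allowed to act on change.** The unadjusted SE is 5.5 x sqrt(2/n), which is 1.697 for n = 21 and 1.556 for n = 25 per group. The adjusted SE multiplies this by sqrt(1 - R2). For R2 = 0.30 and n = 25 it is 1.556 x sqrt(0.70) = 1.302.

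The stated minimization was then simulated with 4,000 trials per cell, testing the T0-T2 change at two-sided 0.05. The Monte Carlo standard error is about 0.003 for type I error (sqrt(0.05 x 0.95/4000)) and up to about 0.006 for power.

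50 children:

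| R2 | Mean model SE, unadjusted | True SD, unadjusted | SE / SD | Type I error, unadjusted | Power, unadjusted | Power, adjusted |
|---|---|---|---|---|---|---|
| 0 | 1.548 | 1.549 | 1.00 | 0.050 | 0.887 | 0.880 |
| 0.10 | 1.552 | 1.491 | 1.04 | 0.041 | 0.882 | 0.904 |
| 0.20 | 1.554 | 1.426 | 1.09 | 0.034 | 0.904 | 0.939 |
| 0.30 | 1.555 | 1.362 | 1.14 | 0.025 | 0.908 | 0.958 |

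The adjusted type I error was 0.050 to 0.057 in these cells. The change in power is -0.7, +2.2, +3.5 and +5.0 points. A separate simulation with 5,000 trials per cell gave -1.1, +1.4, +3.0 and +4.8 points.

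With 42 children the pattern is the same. Unadjusted type I error is 0.050, 0.042, 0.030 and 0.028. Power goes from 0.818 to 0.814, 0.826 to 0.845, 0.841 to 0.888 and 0.841 to 0.920.

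**4. Baseline AHA.** If T0 and T2 have a common SD, the variance of change is 2 SD² (1 - rho), so rho = 1 - 5.5²/(2 SD²). Adjusting for T0 multiplies the variance of the group contrast by (1 + rho)/2. With assumed cross-sectional SDs of 10, 15 and 20 units, rho is 0.849, 0.933 and 0.962, and the multiplier is 0.92, 0.97 and 0.98. The gain is about 2 to 8% of variance. It was worked out without the factors, so it should not simply be added to the gains in step 3.

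**The case against.** The strongest reply is that this is a condensed article, its statistical analysis plan is not shown, and a covariate list is commonly left to that plan. This stands in part. A reader might infer that the primary model contains time, group and their interaction and nothing else. The section says which term is tested. It neither gives a closed formula nor excludes covariates, and the unseen plan may name the factors. The point is therefore a better specification of the described test, not a charge of omission.

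A reader might also infer that power is certainly lost, since the factors plausibly matter for hand function. The documents do not support that. Predicting AHA level is not predicting AHA change, no figure for the latter is given, and at R2 = 0 the unadjusted test is exact while adjustment costs a little power. Nor is the trial short of its own target: the sample size was set without adjustment and delivers its 80%.

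The baseline part is weaker still. The protocol does not say how T0 means are parameterized, and a model with T0 as one of its responses does not ignore baseline. The gain for AHA is small.

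Finally, the factors crossed with three visits add 4 main-effect and 8 interaction parameters in about 50 children. That is true, although only four degrees of freedom bear on the T0-T2 contrast.

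**Conclusion.** The point holds conditionally and is minor. The factors that drive allocation are not named in the described primary test. If they explain 0 to 30% of the variance of AHA change, the unadjusted standard error with 50 children is about 0 to 14% too wide, type I error is about 5% down to 2.5%, and adjustment changes power by about -1 to +5 points (up to about +8 with 42 children). The error is on the conservative side.

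These sizes rest on the assumed R2 and factor prevalences, on the protocol's SD of 5.5, and on a test of the T0-T2 change at two-sided 0.05 without multiplicity correction.

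**What to change.** In the primary AHA mixed model, include age group, MACS level and tactile impairment together with their interactions with time, and constrain the T0 mean to be common to both groups. Main effects alone, added to the model with separate T0 group means, would leave the T0-T2 contrast unchanged with complete data.

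Keep the mixed model as primary, because it uses T1 and retains children with a missing T2. A regression of T2 AHA on group, T0 AHA and the three factors matches it only approximately, and only with complete data. It can serve as a sensitivity analysis.

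State that this adjustment is separate from the predictor covariates. Extend it to continuous secondary outcomes where the model supports it, but not automatically to short ordinal scales such as movement sense (0 to 2) or Goal Attainment Scaling (-3 to 2).

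The cost is analysis wording, four degrees of freedom on the primary contrast (more parameters over three visits), and about 1 power point if the factors are unrelated to change. The factors are recorded at screening and AHA at T0, so no new data are needed. Recruitment is expected to run to June 2027, which leaves time to fix the model in advance.

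### Allocation is minimised on age, MACS level and tactile impairment, but the primary time-by-group model names none of them; if they predict AHA change, the test is conservative and some power is forgone

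*Protocol article*

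**What the plan says.** Sequence generation {16a} of the protocol article assigns children "through randomization by minimization with an allocation ratio of 1:1". The stated purpose is balance: "A minimization technique will be used to enhance homogeneity between both groups". To limit prediction of the next allocation, "an additional random component of 80% probability will be implemented". The factors are age in two levels (split at 11 years), "manual ability (3 MACS-levels: I, II, and III"), and "tactile impairment (2 levels: mild or moderate-severe").

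Statistical methods {20a} analyses primary and secondary outcomes with linear or generalised mixed models. On the random effects it says: "By using random effects, such models correct for the relation among repeated observations within subjects". The treatment comparison is described through its interaction: "interactions between therapy and time will be analyzed to test for differences in improvements over time between both groups (time*group interaction effect"). The section goes on to time trends within each group and pairwise comparisons of visits. It Bonferroni-corrects these for the AHA and singles out T0–T2 as primary.

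The only covariates it names belong to the objective on predictors of response: "somatosensory function at baseline, attentional functioning, and thalamic volume, will be included as covariates in the model for the primary outcome measure". Baseline somatosensory function overlaps with the tactile factor. It is not the allocation stratum, however, and is not presented as an adjustment of the treatment comparison. The items on additional analyses {20b} and on non-adherence and missing data {20c} only refer back to {20a}.

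**The concern.** Minimisation pushes the arms towards equality on its factors. The treatment estimate then varies less from trial to trial than under simple randomisation, to the extent that those factors are prognostic. An analysis that leaves them out does not see this. Its residual variance still contains the between-factor variation, so its standard error is too large, its interval too wide and its true type I error below the nominal level.

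Because the primary contrast is a change within the child, what counts is whether the factors predict **change** in AHA, not its level. What is at stake is precision in a trial of 50 children, together with agreement between the allocation and the prespecified analysis.

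**Working it through.** **1. The plan's own figure.** Sample size {14} uses a difference of 5 AHA units, an SD of change of 5.5, d = 0.9, two-sided alpha 0.05 and power 0.80. For a two-sample t test with n per group, the non-centrality is d × √(n/2), with 2n − 2 degrees of freedom. At n = 20, power is 0.792. At n = 21, the non-centrality is 0.9 × √10.5 = 2.92 and power is 0.812. The stated 21 per group reproduces; at 25 per group power is 0.877. This calculation uses the unadjusted SD of change, so it relies on no adjustment.

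**2. Parameters needed.** Age 1 + MACS 2 + tactile 1 = 4 per visit contrast. With two contrasts against T0 this makes 8 factor-by-time terms.

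**3. Size of the standard error by hand.** With 25 per group, the unadjusted SE of the difference in mean change is 5.5 × √(2/25) = 1.556. Let R² be the share of variance in T0–T2 change explained by the factors. Under perfect balance the true SE is 1.556 × √(1 − R²): 1.476, 1.391 and 1.302 for R² = 0.1, 0.2 and 0.3. The documents give no R², so this range is assumed.

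**4. Simulation of the actual allocation.** Minimisation on marginal totals with a biased coin of 0.80; 4,000 trials per cell; SD of change 5.5; difference 0.9 × 5.5 = 4.95. Assumed: MACS mix 30/45/25%, the other factors 50/50, equal contribution of each factor, no dropout. The T0–T2 change was compared between groups without and with the factors.

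| N | R² | True SE, unadjusted | Model SE, unadjusted | Type I error, unadjusted | Power without → with factors |
|---|---|---|---|---|---|
| 50 | 0 | 1.544 | 1.550 | 4.6% | 87.3% → 86.5% |
| 50 | 0.1 | 1.486 | 1.550 | 4.1% | 87.2% → 88.9% |
| 50 | 0.2 | 1.403 | 1.551 | 3.0% | 89.1% → 92.8% |
| 50 | 0.3 | 1.338 | 1.555 | 2.1% | 90.6% → 95.6% |
| 42 | 0 | 1.703 | 1.684 | 5.0% | 81.2% → 80.1% |
| 42 | 0.1 | 1.632 | 1.689 | 4.3% | 81.8% → 84.0% |
| 42 | 0.2 | 1.550 | 1.687 | 3.0% | 84.1% → 88.7% |
| 42 | 0.3 | 1.499 | 1.693 | 2.8% | 84.2% → 91.6% |

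The true SEs at N = 50 lie close to, and a little above, the perfect-balance values in step 3, as expected with imperfect balance. Simulation error on a type I rate near 5% is √(0.05 × 0.95/4000) = 0.34 points, so the result at R² = 0.1 is only modestly separated from 5%.

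A repeat simulation at N = 50 gave type I error of 3.9%, 3.2% and 1.9% and gains of about 1 to 4 points. Another with 50 allocated and 42 analysed, at a difference of 5 units, gave gains of 2 to 7 points, and a loss from 82% to 80.5% at R² = 0.

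**5. Which terms do the work.** Random-intercept models were fitted to 60 simulated complete data sets with three visits. Adding the factors as main effects left the T2-by-group estimate unchanged to numerical precision, and its SE unchanged to within 0.00003 (mean SE 1.4653 in both). Adding factor-by-time terms did change the result (mean SE 1.4423). Main effects explain level, which the random intercept already absorbs.

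**Limit of the check.** The power and type I figures describe a between-group comparison of T0–T2 change. They do not describe the full sequence in {20a}: overall interaction, then within-group trends, then Bonferroni-corrected pairs.

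**The case against.** The strongest reply is that {20a} is silent on the factors rather than excluding them. It names the interaction to be tested and never says that the model holds nothing else. A full protocol (version 5.2) exists, and an analysis plan may exist; either could list the adjustment terms. This stands in part: it is not shown that the factors will be left out. But {20a} is detailed on testing order, multiplicity, effect sizes and even a covariate list, and someone fitting the model as described would leave out the allocation factors.

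A reader might also infer that the primary test necessarily loses power, that the trial is underpowered, or that its error rate is compromised. The documents support none of these:
- The loss depends on the factors predicting AHA change, for which no figure is given. Differences in AHA level are already absorbed by the random effects, and imbalance in level cancels in a change contrast.
- The error is conservative, so false positives are not inflated.
- The sample size was computed from the unadjusted SD.

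There is some reason to expect prediction of change. Objectives {7} anticipates better response to somatosensory therapy in children with worse somatosensory function, which overlaps with the tactile factor, and the AHA version used depends on age. Neither supplies an R².

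The cost objection also has weight: eight interaction terms are not trivial for coarse ordinal secondary outcomes such as the three-category movement-sense score.

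**Conclusion.** The point holds as a conditional, modest matter of efficiency. The allocation uses three factors that the described primary model does not name. If they explain an assumed 10% to 30% of the variance in T0–T2 AHA change, the unadjusted test runs at a type I error of about 4% to 2%. Adjustment would then recover about 1 to 5 points of power with 50 children, and up to about 7 with 42. If they explain none, the current plan loses nothing and adjustment costs about 1 to 2 points. The analysis remains valid, and the planned 80% power holds in either case. The sizes rest on the assumed R² range and factor frequencies, and on a between-group analysis of change.

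**What to change.** Add one sentence to Statistical methods {20a}, for example:

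> The primary AHA model will include age group, MACS level and tactile impairment category, at the levels used for minimisation, each with its interaction with time, in addition to the time-by-group interaction.

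An alternative, equivalent in purpose with complete data, is to state that the between-group difference in T0–T2 change is adjusted for these three factors. Listing the factors as main effects only would not achieve the aim.

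The factors are established at screening, before randomisation, so no new data are needed. The cost is four extra parameters per visit contrast and about 1 to 2 points of power if the factors turn out not to predict change. Extension to secondary outcomes is optional, particularly for the sparse ordinal scales. If it is wanted, the outcomes concerned should be named in advance.
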